### Follow-up

The participants visit the hospital a total of seven times during the study: the screening visit; visit before baseline; baseline visit; visit 4 (four weeks); visit 5 (eight weeks); visit 6 (12 weeks); and visit 7 (24 weeks). Scheduled tests and evaluations are performed at each visit. The BP control is single-blinded in order to allow identification of the strict BP control and standard BP control groups, because the investigator should check the individual’s target BP during each follow-up. After visit 7, a two-parallel study is performed to confirm the efficacy and safety of the drug in the standard and strict BP control groups. The individuals participate in visits every 12 weeks (36, 48, 60, 72, 84, 96, 108, 120, 132, and 144 weeks) for efficacy and safety assessment (Fig. 2). All of the participants take fimasartan during the open-label study period. The individuals taking losartan during the double-blind study period will be change their drug to the equivalent dose of fimasartan. If the targeted BP cannot be reached, the dose titration method will be used in the double-blind study period (see Fig. 1).

### Blood pressure and biochemical measurements

The reported BP is the mean BP from three measurements on the selected arm. Proteinuria is measured from the spot urine albumin–creatinine ratio (ACR) based on the first urine in the morning. The eGFR is calculated using the modified Modification of Diet in Renal Disease (MDRD) equation [22].

### Primary and secondary endpoints

The primary endpoint is the rate of change in proteinuria in the fimasartan group and the losartan group from baseline to 24 weeks.

The major secondary endpoints are cardiovascular composite endpoints and renal composite endpoints. The cardiovascular composite endpoints are defined as the time to the first occurrence of any of the following (in accordance with the BP control criteria): myocardial infarction; stroke; hospitalization due to heart failure; unstable angina; coronary revascularization; peripheral revascularization; or all-cause mortality. The renal composite endpoints include any of the following (in accordance with the BP control criteria): the time to serum creatinine concentration doubling from baseline; the time to progression to end stage renal disease (ESRD) (as confirmed by the initiation of long-term dialysis or renal transplantation); and all-cause mortality.

### Other secondary endpoints

The other secondary endpoints are summarized as follows: (1) the rate of change in proteinuria in the fimasartan and losartan groups from baseline to weeks 4, 8, and 12; (2) the change in proteinuria in the fimasartan and losartan groups from baseline to weeks 4, 8, and 12; (3) the rate and amount of change in eGFR in the fimasartan and losartan groups from baseline to weeks 4, 8, 12, and 24; (4) the proportion of individuals who developed microalbuminuria (urine ACR < 300 mg/g) in the fimasartan and losartan groups at weeks 4, 8, 12, and 24; (5) the proportion of individuals with ≥ 30% decrease in albuminuria in the fimasartan and losartan groups from baseline to weeks 4, 8, 12, and 24; (6) the proportion of participants with ≥ 50% decrease in eGFR in the fimasartan and losartan groups from baseline to weeks 4, 8, 12, and 24: (7) the rate and amount of change in albuminuria from baseline to weeks 4, 8, 12, 24, 36, 48, 72, 96, 120, and 144 in accordance with the BP control criteria; (8) the rate and amount of change in eGFR from baseline to weeks 4, 8, 12, 24, 36, 48, 72, 96, 120, and 144 in accordance with the BP control criteria; (9) the proportion of individuals with a change in microalbuminuria (urine ACR < 300 mg/g) at weeks 4, 8, 12, 24, 36, 48, 72, 96, 120, and 144 in accordance with the BP control criteria; (10) the proportion of participants with ≥ 30% decrease in albuminuria from baseline to weeks 4, 8, 12, 24, 36, 48, 72, 96, 120, and 144 in accordance with the BP control criteria; and (11) the proportion of individuals with ≥ 50% decrease in eGFR from baseline to weeks 4, 8, 12, 24, 36, 48, 72, 96, 120, and 144 in accordance with the BP control criteria.

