### Study eligibility

#### Inclusion and exclusion criteria

Patients are screened for the following four required conditions: high BP; CKD; overt proteinuria (or macroalbuminuria); and type 2 diabetes mellitus. The detailed inclusion criteria are described in Table 1. The exclusion criteria are described in Table 2. Finally, after learning about the study, patients voluntarily provided written consent to participate.

**Table 1 Tab1:** Inclusion criteria

Age: 19–70 years
Screening visit (Visit 1)
Hypertension in treatment-naïve patients
140 mmHg ≤ SBP < 180 mmHg and DBP < 110 mmHg
Hypertension with treatment, including ACEI/ARB
130 mmHg ≤ SBP < 180 mmHg and DBP < 110 mmHg
eGFR ≥ 30 mL/min/1.73 m^2^ (by MDRD) within the past six months
Urine protein (within the past six months)
ACR ≥ 300 mg/g (or mg/day)
or protein–creatinine ratio ≥ 500 mg/g (or mg/day)
Type 2 diabetes mellitus (diagnosed > 3 months prior) on medications with
no changes in medication regimen/dose within the last three months
Baseline visit (Visit 3)
Hypertension
140 mmHg ≤ SBP < 180 mmHg and DBP < 110 mmHg
eGFR ≥ 30 mL/min/1.73 m^2^ (by MDRD)
Urine protein: ACR ≥ 300 mg/g in spot urine
Type 2 diabetes without regimen change during placebo run-in period

*SBP* systolic blood pressure, *DBP* diastolic blood pressure, *ACEI* angiotensin converting enzyme inhibitor, *ARB* angiotensin receptor blocker, *ACR* albumin–creatinine ratio, *eGFR* estimated glomerular filtration rate, *MDRD* Modification of Diet in Renal Disease

**Table 2 Tab2:** Exclusion criteria

Secondary or malignant hypertension
Inter-arm BP difference: SBP > 20 mmHg or DBP > 10 mmHg
Symptomatic orthostatic hypotension
Cardiovascular history
MI, congestive heart failure (NYHA class III or IV), CABG, PTCA, or angina < 3 months before enrollment
Severe cerebrovascular disease (stroke, cerebral infarction, or cerebral hemorrhage)
Arrhythmia (significant ventricular tachycardia, atrial fibrillation, or atrial flutter)
Significant valvular disease: aortic stenosis or mitral stenosis
Hypertrophic cardiomyopathy
Type 1 DM or HbA1c > 9% at screening
Significant renal or hepatic disease
Dialysis, cirrhosis, biliary tract obstruction, cholestasis, or liver failure
eGFR (MDRD) < 30 mL/min/1.73 m2, hyperkalemia (>5.5 mmol/L) or hypokalemia (<3.5 mmol/L)
AST or ALT > 3 times the upper limit of normal

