### Statistics

In order to achieve a statistical power of 80%, the sample size assumed a non-inferiority margin of 18% (based on two-sided t test and a significance level of 0.025). This is based on the rate of change in proteinuria from baseline (Week 0) to week 24 of both losartan and fimasartan groups with a standard deviation of 62% [10, 12–14, 23]. Based on the assumption of a drop-out rate of 20%, a total of 468 patients are needed for randomization (with 234 patients per treatment arm).

The primary efficacy assessment finds that the fimasartan group is not inferior to the losartan group if the lower limit of a 95% two-sided confidence interval for the difference in the rate of change in proteinuria at week 24 between the fimasartan and losartan groups (control group - study group) is > − 18%. This is defined as the non-inferiority margin.

The major secondary efficacy assessment is determined by the incidence of combined cardiovascular and renal composite endpoints and is assessed using Kaplan–Meier curves, according with target BP at 144 weeks. The median survival time and confidence interval for the median survival time are presented. The log-rank test is used to compare the groups. Other secondary efficacy assessments are determined using the following methods. For continuous variables, descriptive statistics (number of individuals, mean, standard deviation, median, minimum, and maximum) for each time point are provided according to treatment group or the BP control criteria. The t-test is used to compare the inter-group difference in the rate of change. The inter-group difference in the amount of change is tested using the analysis of covariance, with the baseline values as covariates and the treatment groups as factors. The least squared mean and standard error are provided for each group. Frequencies and ratios are provided for categorical variables such as the proportion of individuals. For categorical variables, the Chi-square test, Fisher’s exact test, or Cochran–Mantel–Haenszel test is performed.

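### The microalbuminuria endpoint uses the entry cut-off of 300 mg/g, so some single-visit responders are measurement noise; adjust the comparison for baseline ACR (minor)

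*Protocol article*

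**What the plan says.** Entry (Protocol article, Table 1). At the baseline visit: "Urine protein: ACR ≥ 300 mg/g in spot urine". At screening, a value from the past six months must also qualify, either "ACR ≥ 300 mg/g (or mg/day") or a protein–creatinine ratio of at least 500 mg/g.

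Response (Other secondary endpoints). Item (4) is defined as "the proportion of individuals who developed microalbuminuria (urine ACR < 300 mg/g) in the fimasartan and losartan groups at weeks 4, 8, 12, and 24". Item (9) is defined as "the proportion of individuals with a change in microalbuminuria (urine ACR < 300 mg/g"), at ten time points to week 144, by blood-pressure target. Size of fall is a separate endpoint, item (5): "the proportion of individuals with ≥ 30% decrease in albuminuria in the fimasartan and losartan groups from baseline"; item (10) is its counterpart for the blood-pressure groups.

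Measurement (Blood pressure and biochemical measurements): "Proteinuria is measured from the spot urine albumin–creatinine ratio (ACR) based on the first urine in the morning".

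Analysis (Statistics): "For categorical variables, the Chi-square test, Fisher’s exact test, or Cochran–Mantel–Haenszel test is performed". No stratification variable is named for the last of these tests.

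**The concern.** A patient is admitted at or above 300 mg/g and is a responder at any visit where the value is below 300. As the rule is stated, a change from 310 to 290 mg/g (20/310, about 6%) is a response, while a change from 2000 to 400 mg/g (an 80% fall) is not. Patients are selected on a high baseline reading, so repeat readings tend to move down, towards response, even if nothing has changed.

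Two things are at stake. The proportion reported in any one arm includes responders who owe nothing to treatment. And the unadjusted comparison of proportions is blunter than it need be, because much of the variation in who crosses 300 is explained by how far above 300 the patient started.

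**Working it through.** **1. The plan's own figure.** The protocol gives no number for this endpoint. Its sample size is for the primary endpoint: "non-inferiority margin of 18% (based on two-sided t test and a significance level of 0.025"), SD 62%, power 80%, drop-out 20%.
- n per arm = 2 × (1.960 + 0.842)² × 62² / 18² = 186.2, so 187.
- 187 / 0.80 = 233.75, so 234 per drug arm and 468 in total. This matches. It matches with 0.025 taken as one-sided, which agrees with the stated 95% two-sided interval.
- So 187 evaluable patients per drug arm is the base used below.

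**2. Noise for one patient.** With log-normal readings, P(reading < 300) = Φ[ln(300/true ACR) / s], where s = √ln(1 + CV²). The within-person CV of 20 to 50% is assumed.

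| Underlying ACR (mg/g) | P(reading < 300), CV 20% to 50% |
|---|---|
| 300 | 50% |
| 350 | 22% to 37% |
| 400 | 7% to 27% |
| 500 | 0.5% to 14% |
| 1000 | 0% to 0.5% |

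The problem is confined to patients who start near the cut-off.

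**3. Noise for the trial, no treatment effect.** Two sets of assumptions were simulated. Neither is in the protocol.

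*Set A:* underlying median ACR 500, 800 or 1200 mg/g; between-person log SD 0.8 or 1.0; CV 20 to 50% (s from 0.20 to 0.47).
- Baseline value alone qualifying: 1.4% to 14.1% responders at a visit.
- Screening and baseline both qualifying (screening treated as an ACR): 0.8% to 9.4%, that is 0.008 × 187 ≈ 2 to 0.094 × 187 ≈ 18 patients per drug arm.
- For scale, with both values qualifying and every patient truly falling by 30%: 5.4% to 21.2%.

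*Set B:* per-sample SD taken from the plan's 62%. Log SD of change = √ln(1 + 0.62²) = 0.570; per sample 0.570/√2 = 0.403. Between-person log SD 0.8; underlying median 500, 700 or 1000.
- Both values qualifying, SD 0.40: 7.8%, 5.2%, 3.0%.
- Baseline only, SD 0.40: 12.0%, 7.8%, 4.4%.
- SD 0.3 to 0.5, either entry rule: 2% to 15%.

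Together: roughly 1 to 15%.

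**4. Does a minimum fall cure it?** Only partly. In set A, adding a fall of at least 30% at the same visit lowers 0.8–9.4% to 0.4–8.2% (both values qualifying). In set B at SD 0.40 and median 500, a re-run gave 6.4% instead of 7.8%.

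**5. What baseline adjustment gains.** Assumed true ACR ratios to baseline of 0.65 and 0.80 in the two arms, 187 per arm, two-sided 0.05, both values qualifying. Power from 2,000 simulated trials per cell for single-visit ACR < 300, unadjusted test then logistic regression with log baseline ACR:

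| Median (mg/g) | SD 0.3 | SD 0.4 | SD 0.5 |
|---|---|---|---|
| 500 | 71% → 83% | 58% → 67% | 48% → 54% |
| 600 | 65% → 77% | 54% → 61% | 48% → 53% |
| 1000 | 45% → 54% | 36% → 42% | 34% → 37% |

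The gain is about 7 to 11 points for SD 0.3 to 0.4 (6 to 12 in single cells) and 3 to 6 points at SD 0.5. For the fall of at least 30%, it is 0 to 2 points at SD 0.3 to 0.4 and 2 to 3 at SD 0.5.

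**The case against.** **The shared cut-off is inherent.** Patients enter with macroalbuminuria, so leaving that category means ACR < 300. The 310-to-290 contrast can be made against any category endpoint, and the size of change is covered by the primary endpoint and items (1), (2), (5), (7) and (10). This stands: it is a reason to keep the endpoint and interpret it with care. It does not remove the noise or justify an unadjusted test.

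**The article is condensed.** The full protocol may require a repeat sample. That also stands, so absence of confirmation is not charged as an error; the figures apply to the rule as stated.

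**Noise is common to randomised arms.** This stands and limits the point. A reader might infer that noise responders cannot be separated from drug effect because there is no placebo arm. Losartan is a concurrent, randomised, double-blind control, so similar noise rates cancel in the difference; only the absolute proportions are inflated. A reader might also infer that dilution pushes the trial towards a non-inferiority claim. The 18% margin applies only to the primary rate of change. These items get ordinary tests of difference, where dilution is conservative.

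**The magnitude could be lower.** The 62% is the SD of change on treatment and includes real differences in response, so 0.40 per sample is towards the high side. Some patients are screened on an ACEI or ARB that is then stopped. If that made screening ACR 30% lower, the set B rates of about 7.8, 5.1 and 3.0% become 5.0, 3.2 and 1.9%. Against this, the screening value may be up to six months old or be a protein–creatinine ratio, a weaker filter than modelled. The chance of crossing 300 at least once by week 24 (8 to 27% at SD 0.40) is not the endpoint, which is a proportion at each week.

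**Cochran–Mantel–Haenszel could adjust for baseline.** It could, and covariate choice is often left to the SAP. But no baseline stratifier is named, and the chi-square and Fisher alternatives do not adjust.

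**Conclusion.** The point holds as a minor one. Items (4) and (9) use the entry threshold, so a share of single-visit responders reflects sampling variation and regression to the mean: roughly 1 to 15% per visit with no effect, towards the lower end when the screening value also qualified. That some such responders occur follows from the rule and any within-person variation near 300. How many depends on the assumed ACR distribution and per-sample SD, which the protocol does not give.

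The consequence is inflated absolute proportions and some loss of power in the drug and blood-pressure-target contrasts, without bias in either. The primary endpoint, its non-inferiority test and N = 468 are unaffected. The documents plan no single-arm remission claim from these items; the caution is against reading them that way later.

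**What to change.** - For items (4), (5), (9) and (10), replace the unadjusted chi-square or Fisher comparison by logistic regression with treatment (or blood-pressure target) and log baseline ACR. The odds ratio is conditional on baseline; standardise it to a risk difference for reporting.
- As a supportive analysis for (4) and (9), report the proportion with ACR < 300 mg/g and a fall of at least 30% from baseline at the same visit. Its proportions will be slightly lower, and it reduces the noise without removing it.
- State that proportions within one arm are not to be read as remission due to treatment.
- Do not make a two-visit mean the definition. It changes the quantity estimated, and at week 36 it would average a blinded-period value (losartan for about half the patients) with an open-label fimasartan value. At most, use weeks 12 and 24 as a sensitivity analysis at week 24.

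Cost: analysis wording only; no new samples, visits or patients. The article reports recruitment still open at 171 randomised, so the change could be fixed before unblinding.

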### Safety assessment

The safety assessments include laboratory tests (hematology/blood chemistry, urinalysis), electrocardiogram, chest X-ray, physical examination, orthostatic hypotension assessment, and changes in body weight and pulse rate. At least once after randomization, any adverse events that occurred after administration of the investigational product are assessed. All adverse events are summarized and presented by treatment group with respect to severity, relationship to the investigational product, and outcome.

### Data collection and management

The electronic case report form (eCRF) is developed by supervision of Boryung pharm’s data management (DM) team before first enrollment. Data entry will be performed by the investigators and clinical research coordinators at the participating sites using a web-based database: Medidata Rave™ (Medidata Solutions, Inc., http://www.mdsol.com). Rave™ is a commercial system designed to capture, manage, and report clinical research data. And Medidata Rave™ supports electronic record and electronic signature requirements, audit trail including US 21 CRF part 11. Through this system, each participating site is assigned a unique code, as identified by the study team. All staff is trained in using eCRF in advance and then is given each EDC (Electronic Data Capture)’s role. The DM team also provided at each site on the data entry and data monitoring guide book. All participating sites will use the same CRFs. If responses to the initial inclusion and exclusion criteria provided by the individual performing the data entry fulfill study criteria, the system will dynamically generate randomization and data validation process. All DM tasks are performed by Data Management Plan (DMP). We designed the eCRF and set up all DM process according the protocol and DMP documents. The DMP include all staff’s role and responsibility, each step’s definition and process, data backup and transfer, etc. Auto and manual data queries are generated by CRA (Clinical Research Associates) or a DM person and will be resolved by CRCs (Clinical Reseach Coordinators) and investigators. Through this iterative process, we will make the data clean and finally perform database lock. All database backup of eCRF will be done in real time by Medidata’s Houston data center and Boryung pharm’s database system.

### Statistics

In order to achieve a statistical power of 80%, the sample size assumed a non-inferiority margin of 18% (based on two-sided t test and a significance level of 0.025). This is based on the rate of change in proteinuria from baseline (Week 0) to week 24 of both losartan and fimasartan groups with a standard deviation of 62% [10, 12–14, 23]. Based on the assumption of a drop-out rate of 20%, a total of 468 patients are needed for randomization (with 234 patients per treatment arm).

The primary efficacy assessment finds that the fimasartan group is not inferior to the losartan group if the lower limit of a 95% two-sided confidence interval for the difference in the rate of change in proteinuria at week 24 between the fimasartan and losartan groups (control group - study group) is > − 18%. This is defined as the non-inferiority margin.

The major secondary efficacy assessment is determined by the incidence of combined cardiovascular and renal composite endpoints and is assessed using Kaplan–Meier curves, according with target BP at 144 weeks. The median survival time and confidence interval for the median survival time are presented. The log-rank test is used to compare the groups. Other secondary efficacy assessments are determined using the following methods. For continuous variables, descriptive statistics (number of individuals, mean, standard deviation, median, minimum, and maximum) for each time point are provided according to treatment group or the BP control criteria. The t-test is used to compare the inter-group difference in the rate of change. The inter-group difference in the amount of change is tested using the analysis of covariance, with the baseline values as covariates and the treatment groups as factors. The least squared mean and standard error are provided for each group. Frequencies and ratios are provided for categorical variables such as the proportion of individuals. For categorical variables, the Chi-square test, Fisher’s exact test, or Cochran–Mantel–Haenszel test is performed.

The safety analysis is based on adverse events, laboratory abnormalities, electrocardiography, chest X-rays, orthostatic hypotension assessments, and abnormal changes in body weight and pulse. Appropriate statistical analysis methods are used to compare groups with regard to differences in the rate of adverse events, abnormal laboratory values, or other parameters. Either the Chi-square test or Fisher’s exact test is used to assess differences in the incidence of adverse events between the groups. Continuous data, including laboratory values (hematology/blood chemistry, urinalysis) and vital signs (pulse rate, body weight, etc.), are presented in the form of descriptive statistics (mean, standard deviation, minimum, maximum, and median) by group and visit. Either a paired t-test or the Wilcoxon signed-rank test is used to test the intra-group difference in the continuous data between baseline and after drug administration. In addition, the two-sample t-test and Wilcoxon rank sum test is performed to test inter-group differences (in continuous variables) from baseline to after drug administration. Among all of the laboratory values, categorical data are divided into normal and abnormal results. The inter-group differences are tested using the Chi-square test or Fisher’s exact test. The McNemar’s test is used to compare differences in the categorical data between baseline and after drug administration.

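### The sample-size sentence misstates the level of the primary test: a two-sided test at 0.025 matches neither the planned 468 patients nor the 95% confidence-interval rule, which both correspond to one-sided 0.025

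*Protocol article*

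**What the plan says.** All the relevant text is in the Statistics section of the protocol article.

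- **Level and sidedness, sample-size sentence:** "based on two-sided t test and a significance level of 0.025", with a target power of 80%.
- **Margin:** "the sample size assumed a non-inferiority margin of 18" (per cent).
- **Variability:** "both losartan and fimasartan groups with a standard deviation of 62" (per cent), for the rate of change in proteinuria from baseline to week 24.
- **Result, after a 20% drop-out allowance:** "a total of 468 patients are needed for randomization (with 234 patients per treatment arm".
- **Decision rule, next paragraph:** non-inferiority is concluded if the "lower limit of a 95% two-sided confidence interval for the difference in the rate of change in proteinuria at week 24" (losartan minus fimasartan) lies above −18%.

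The section does not state the true difference between the drugs that was assumed for the calculation.

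**The concern.** A two-sided 95% confidence interval, judged on its lower limit alone, is a one-sided test at 0.025. A two-sided test at 0.025 has 0.0125 in each tail, and its matching interval is 97.5%. The sample-size sentence and the decision rule therefore give two different error rates for the trial's only primary claim.

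The type I error rate is one of the figures on which a non-inferiority claim rests. A reader should be able to take it from the text. Here the intended value can be recovered only by recalculating the sample size or by letting the decision rule override the sample-size sentence.

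**Working it through.** **Inputs.** From the Statistics section: margin 18, standard deviation 62 in both arms, power 80%, drop-out 20%, 234 randomised per drug arm. Assumed: true difference 0, which the article does not state.

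**Formula.** Evaluable patients per arm, normal approximation:

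n = 2 × (z_α + z_power)² × SD² / margin², with z_power = 0.8416. Randomised per arm = n / (1 − 0.20).

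Here 2 × 62² / 18² = 7688 / 324 = 23.73.

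**Step 1: reproduce the plan's figure, one-sided 0.025 (z = 1.960).**
n = 23.73 × (1.960 + 0.8416)² = 186.2, rounded up to 187. Then 187 / 0.8 = 233.75, rounded up to 234 per arm and **468 in total**. This matches exactly. Two-sided 0.05 uses the same z and gives the same answer. The noncentral t version gives 188 evaluable and 235 randomised per arm (470), a negligible difference.

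**Step 2: the wording taken literally, two-sided 0.025 (z = 2.241).**
n = 23.73 × (2.241 + 0.8416)² = 225.5, rounded up to 226. Then 226 / 0.8 = 282.5, rounded up to 283 per arm and **566 in total**. This does not match.

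**Step 3: other variants.** One-sided 0.05 gives 147 evaluable, 184 randomised per arm, 368 in total. Applying drop-out as n × 1.2 gives 225 per arm at one-sided 0.025 and 272 at one-sided 0.0125. None gives 234.

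**Step 4: power with 187 evaluable per arm.** The standard error is 62 × √(2/187) = 6.41, and 18 / 6.41 = 2.807.

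| Level applied | Power, normal | Power, t |
|---|---|---|
| One-sided 0.025 (the 95% interval rule) | 80.2% | 80.0% |
| Two-sided 0.025 (literal wording) | 71.4% | 71.1% |

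**Step 5: effect on the decision boundary.** With this standard error, the 95% interval rule accepts an observed fimasartan deficit of up to 18 − 1.960 × 6.41 = 5.4 points. A 97.5% interval would accept up to 18 − 2.241 × 6.41 = 3.6 points. The gap is 1.8 points.

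**Step 6: how much rests on the assumed difference of 0.** For two-sided 0.025 to give 187 evaluable per arm, margin plus assumed advantage would have to equal (2.241 + 0.8416) × 6.41 = 19.8. That is an assumed true advantage for fimasartan of about 1.8 points. The article states no such assumption, whereas 0 reproduces 468 with nothing added. The mismatch between the stated level and the 95% interval does not depend on this assumption.

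**The case against.** The strongest reply is that nothing of substance is wrong. The article gives one primary decision rule, the 95% interval, and under it 468 patients deliver the stated 80% power. The test and its level appear in a parenthesis within the sample-size sentence and are not presented as a second analysis of the primary endpoint. The t-test named later in the section is for other secondary assessments. The likeliest history is that 0.025 is the per-tail level and that the word two-sided was carried over from the confidence interval.

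Most of this stands, and it rules out two stronger readings that a reader might infer:

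- **That the trial is underpowered at 71%.** That figure needs a 97.5% interval, which the article nowhere proposes. It also needs a true difference of 0 and 187 evaluable per arm. With all 234 per arm evaluable, literal power would be about 81% to 82%, although 234 already includes the drop-out allowance.
- **That two planned analyses could give opposite verdicts.** An observed deficit between 3.6 and 5.4 points would be judged differently only if the parenthesis replaced the stated rule. Only one rule is set.

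What does not stand is that the sentence needs no correction. It gives a specific level and a specific sidedness, the combination disagrees with the rest of the section, and no other part of the article corrects it. Because the article does state these items, this is not a detail left to the full protocol or analysis plan.

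**Conclusion.** The stated level of the primary test is wrong as written. The planned number and the decision rule both correspond to one-sided 0.025 (two-sided 0.05); the sample-size sentence alone says two-sided 0.025. The reproduction of 468 rests on an inferred true difference of 0 and on 20% drop-out applied by division.

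The size of the problem is limited. It is a misstatement of the error rate of the primary claim, not a shortfall in sample size. The literal consequences (about 71% power, or 98 more patients, 566 − 468) are conditional on applying a test that the decision rule does not use. The correction is still worth making because it concerns the type I error of the only primary comparison.

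**What to change.** In the sample-size sentence, state a one-sided t test at a significance level of 0.025, equivalent to using the lower limit of the two-sided 95% confidence interval. Giving the level as two-sided 0.05 would repair it equally well; the one-sided form matches the decision rule more directly.

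In the same sentence, the sponsor should confirm and state the true difference assumed between the drugs. A value of 0 reproduces the sample size, but it should be recorded as the sponsor's assumption and not left to be inferred.

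Keep 468 patients, 80% power, the margin of 18% and the 95% interval rule unchanged. The cost is a wording correction. The Trial status section reports recruitment as ongoing, with 171 patients randomised, so the correction could be made without affecting the conduct of the trial.
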